#### Plans for collection, laboratory evaluation and storage of biological specimens for genetic or molecular analysis in this trial/future use {33}

Not applicable, no laboratory evaluation and storage of biological specimens for genetic or molecular analysis in this trial.

### Statistical methods

#### Statistical methods for primary and secondary outcomes {20a}

In line with the recommendations of Baldwin [45], we will apply a multilevel modeling approach to address the nested data structure (sessions at level 1 nested within patients at level 2 nested within therapists at level 3). Thereby, we will treat time as a within-subject (level 1) factor and treatment condition as a between-subject (level 2) factor. Our statistical hypothesis that we expect a stronger reduction of psychopathological symptomatology in the IG-M than in the CG-R and the CG implies a statistically significant interaction effect between group (IG-M vs. CG-R vs. CG) and time. Our hypothesis that the mindfulness condition moderates the relationship between therapeutic alliance and symptomatic outcome implies a significant cross-level interaction between group and therapeutic alliance in predicting (time-varying) symptom severity. Moreover, patients’ and therapists’ pre-treatment characteristics will be investigated as predictors at levels 2 and 3 to control for differential effects on the outcome in the three treatment arms.

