### Objectives {7}

The main purpose of the study is to investigate whether session-introducing mindfulness interventions (SIMI) in comparison to session-introducing relaxation interventions (SIRI) and no specific intervention at the beginning of individual psychotherapy sessions with children and adolescents between 11 and 19 years of age have a positive impact on the therapeutic process. Session-introducing intervention means that in the first 5 to 10 min of a 50-min therapy session, either a short mindfulness intervention, or a short relaxation intervention, or no specific intervention (but the proceeding as usual) will be conducted. This session-introducing intervention could foster self-acceptance and help to focus attention on the present moment of the session, therefore strengthening the therapeutic alliance and outcome effects. Specifically, we want to investigate if SIMI in comparison to SIRI and no intervention at the beginning of psychotherapy sessions lead to a reduction in psychopathological symptomatology and to an improvement of the therapeutic alliance. Furthermore, we hypothesize that the mindfulness condition moderates the relationship between therapeutic alliance and symptomatic outcome. Before the start of therapeutic treatment, patients will be randomized either to the intervention group, practicing SIMI at the beginning of the therapy sessions (IG-M), or to the active control group, practicing SIRI at the beginning of the therapy sessions (CG-R), or to the control group with no specific interventions at the beginning of the therapy sessions (CG). We will investigate the following hypotheses:

H1) We hypothesize that patients of the IG-M will improve more in symptomatic outcome in comparison to the CG-R and CG.

H2) We hypothesize that both patients and therapists of the IG-M will experience stronger increases of therapeutic alliance across the course of therapy in comparison to the CG-R and CG.

H3) We hypothesize that the mindfulness condition moderates the relationship between therapeutic alliance and symptomatic outcome.

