#### Primary outcome measures

The primary outcome of the study is patients’ general psychopathological symptomatology (assessed by the total score of the Youth Self-Report 11-18R (YSR 11-18R; [42]). The total score of the YSR-11-18R comprises items related to symptoms of anxiety, depression, somatic complaints, social problems, thought problems, attention problems, rule-breaking behavior, and aggressive behavior [42]. The YSR 11-18R will be assessed before the start of therapy (pre), at the 3rd therapy session (mid-S_3_), at the 10th therapy session (mid-S_10_), at the 17th therapy session (mid-S_17_), at the 24th therapy session (post), and at 6-month follow-up (for more details, see Table 1). Of primary interest are change trajectories of the general psychopathology over the course of therapy. We will assess and compare change trajectories of the three treatment conditions using multilevel-models.

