#### Sample size {14}

A recent meta-analysis has detected small to medium effects of MBIs in RCTs with youth in depression (*d* = 0.27), anxiety (*d* = 0.16), executive functions (*d* = 0.30), and attention (*d* = 0.19) [24]. A meta-analysis that has analyzed the effects of meditation in non-clinical groups of adult meditators has detected moderate effect sizes for meditation compared to relaxation (*r* = .21) on psychological outcomes [43].

Taking these results into account, power analyses with G*Power [44] for the detection of small to medium-sized effects (Cohen’s *f* = 0.12) for the interaction between time (pre, T3, T10, T17, T24) and treatment condition (IG-M vs. CG-R vs. CG) (analysis of variance (ANOVA) repeated measures, within-between-interaction, *α* = 0.05, power (1 − β) = 0.80, number of groups = 3, number of measurements = 5, pre–post correlation *r* = 0.5, nonsphericity correction = 1) for the YSR 11-18R total score primary outcome resulted in a sample size of 108 patients. Although this should only be seen as a proxy for the power of the reported multilevel models (MLMs), previous research showed that power in MLM is often comparable to (or even higher than) power in an ANOVA design [45, 46]. The planned sample size should, therefore, be considered a conservative estimate required to detect a small to medium sized condition × time interaction. Taking a drop-out-rate of about 25% into account (i.e., 27 patients), a total sample of 135 patients will be assigned to one of the three treatment groups by a stratified randomization process.

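### The only test named and powered for H1 is the non-directional three-arm group-by-time interaction, so the stated 80% is not power for mindfulness beating both controls

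*Protocol article*

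**What the plan says.** Objectives {7} gives H1 as: "patients of the IG-M will improve more in symptomatic outcome in comparison to the CG-R and CG". That is a direction against each of two named comparators.

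Statistical methods {20a} restates the hypothesis in the same direction and then says that it "implies a statistically significant interaction effect between group (IG-M vs. CG-R vs. CG) and time". Primary outcome measures adds only: "We will assess and compare change trajectories of the three treatment conditions using multilevel-models".

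Sample size {14} is calculated for "small to medium-sized effects (Cohen’s *f* = 0.12) for the interaction between time" and condition. The procedure is an ANOVA, "repeated measures, within-between-interaction", with "number of groups = 3, number of measurements = 5", alpha 0.05, correlation 0.5, nonsphericity correction 1 and "power (1 − β) = 0.80". This gives 108 evaluable patients. The section describes the ANOVA as a proxy for the multilevel models.

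No section names an IG-M versus CG-R or IG-M versus CG contrast, or says whether one or both comparisons must succeed.

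**The concern.** H1 entails a group-by-time interaction, but an interaction does not entail H1. The overall test responds to any divergence among the three trajectories, whichever arm causes it and in whichever direction. It cannot separate mindfulness beating both controls from mindfulness and relaxation being equally good, or from relaxation alone working.

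Two things are at stake. The sample size justification offers 80% power for a question that is not the one H1 asks. And the comparison with established interventions, which Aim of the present study lists as its second aim, has no stated test, error rate or power.

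**Working it through.** **Inputs.** From Sample size {14}: f = 0.12, k = 3 groups, m = 5 occasions, correlation ρ = 0.5, alpha 0.05, N = 108. From Sequence generation {16a}: equal allocation, so n = 36 per arm. Assumed here: linear divergence from pre to session 24, compound symmetry, SD 1 at each occasion, no therapist clustering.

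**1. The plan's own figure.** For the within-between interaction:
- λ = N·m·f²/(1 − ρ) = 108 × 5 × 0.0144/0.5 = 15.55
- df1 = (3 − 1)(5 − 1) = 8; df2 = (108 − 3)(5 − 1) = 420
- Power from the noncentral F = 0.808

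The smallest N that reaches 0.80 is 107, and 108 is the next multiple of 3. The stated figure reproduces.

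**2. What that test can distinguish.** Under linear divergence λ = n·S·Σ(b_j − b̄)²/(1 − ρ). Here b_j is arm j's pre-to-session-24 change and S is the sum of squared centred times, scaled so that pre to session 24 equals 1. Relabelling the arms or reversing the sign leaves Σ(b_j − b̄)² unchanged, so power is unchanged. When one arm differs from the other two by D, Σ = (2/3)D².

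With occasions at sessions 0, 3, 10, 17 and 24, S = 0.678. Then f = 0.12 corresponds to D = √(15.55 × 0.5/(36 × 0.667 × 0.678)) = 0.69 SD. With equally spaced occasions S = 0.625 and D = 0.72 SD. The power of the interaction is the same either way.

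| True pattern | H1 true? | Interaction significant | Both slope contrasts favour IG-M |
|---|---|---|---|
| IG-M > CG-R = CG | yes | about 81% | about 87% |
| IG-M = CG-R > CG | no | about 81% | about 2.5% |
| CG-R > IG-M = CG | no | about 81% | about 0% |

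Simulations of the same ANOVA (up to 20,000 trials per pattern) gave 80% to 81% in the third column, and also when IG-M was the worst arm.

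**3. Power for H1 itself.** Variances at 36 per arm, using the session times:
- Slope difference: (2/36)(1 − ρ)/S = 0.0278/0.678 = 0.0409, SE 0.202
- Difference in session-24-minus-pre change: (2/36) × 2(1 − ρ) = 0.0556, SE 0.236

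The two contrasts share the IG-M arm, so they correlate 0.5. Power is the bivariate normal probability that both exceed 1.96.

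- CG-R = CG: both differences are 0.69. Slopes: 0.69/0.202 = 3.42, power per contrast 0.927, both 0.875. Change score: 0.69/0.236 = 2.93, per contrast 0.834, both 0.735.
- Arms evenly spaced with CG-R midway: Σ = D²/2, so f = 0.12 gives D = 0.80 for IG-M versus CG and 0.40 for IG-M versus CG-R. Slopes: 0.40/0.202 = 1.97, power against relaxation 0.505, both 0.503. Change score: 0.40/0.236 = 1.69, power against relaxation 0.395, both 0.388.

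In the evenly spaced pattern, 0.80 for both slope contrasts would take about 73 per arm, or 3 × 73 = 219 evaluable patients.

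**The case against.** The strongest reply is textual. The plan says that H1 implies an interaction, which is correct. It nowhere says that a significant interaction is enough, or that H1 would be accepted without looking at direction. A reader might infer that the trial will declare H1 on the overall test alone; the document does not support that. It follows that the 81% under the false-H1 patterns is not a type I error rate. It is the power of a valid test to detect a real difference lying in another arm, and it would become a false claim for mindfulness only under a decision rule that the plan does not state. Nor would a significant interaction count for nothing: it would be insufficient for H1, not irrelevant to it.

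Second, the 8-df test belongs to the ANOVA, which the plan calls a proxy. A multilevel model coded with IG-M as reference would yield both pairwise slope differences directly, and nothing excludes that coding. Contrast coding and testing order are also commonly left to an analysis plan, so their absence from an article would not by itself be a finding.

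These replies stand, and they narrow the point. They do not remove it: the article names one test for H1 and bases its sample size on that test, and the test does not match the hypothesis. Contrasts added in an analysis plan would still leave the stated 80% attached to something else.

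Third, requiring both contrasts is one reading among several; two separately reported comparisons would be another. That is fair as a design choice, but H1 as worded claims superiority to both controls and is supported only if both hold.

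**Conclusion.** The point holds as a mismatch between H1 and the only test named and powered for it. The interaction is necessary but not sufficient, and the 80% is power for some difference among the three arms. That part follows algebraically and needs no assumption about the data.

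Power for H1 as worded depends on where relaxation falls. At 36 per arm and f = 0.12 it is about 0.87 (slopes) or 0.73 (session-24-minus-pre change) if CG-R equals CG, and about 0.50 or 0.39 if the arms are evenly spaced. These figures rest on linear divergence, compound symmetry with correlation 0.5 and no therapist clustering. Relaxation is chosen as an established active comparator in Explanation for the choice of comparators {6b}, so an intermediate position for CG-R cannot be set aside, and the favourable figures should not be quoted alone.

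**What to change.** In Statistical methods {20a}, state that H1 is judged on two pre-specified contrasts from the same multilevel model: IG-M minus CG-R and IG-M minus CG, in change over time. Say whether change means slope or session 24 minus pre. Test each at two-sided 0.05, and state that H1 is supported only if both favour IG-M. Because both are required, no alpha split is needed. Keep the interaction as a supporting test.

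In Sample size {14}, say that 0.80 applies to the overall interaction, and give power for the two contrasts under both an equal-controls and an evenly spaced pattern.

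The change needs wording and contrast code; design, data collection and enrolment are untouched. The price is a less favourable stated power that varies with the pattern, down to about 0.50 or 0.39 when relaxation lies midway. The 219 evaluable patients above show the size of that gap and are not a request to enrol more.

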#### Interim analyses {21b}

To the present date, no interim analyses are planned. The results of the study preparation workshops for the trainee therapists will be analyzed before MARS-CA termination. Decision to terminate the trial is up to the authors.

#### Methods for additional analyses (e.g., subgroup analyses) {20b}

To the present date, no additional analyses such as subgroup analyses are planned. In principle, additional analyses are possible.

#### Methods in analysis to handle protocol non-adherence and any statistical methods to handle missing data {20c}

According to the revised CONSORT statement, statistical analyses will be conducted by an intention-to-treat as well as a completer analysis [47]. Missing data will be handled according to the most recent guidelines for multilevel analyses.

#### Plans to give access to the full protocol, participant level-data, and statistical code {31c}

The MARS-CA protocol is available for the public under clinicaltrials.gov. Final trial data set and statistical code will be available from the corresponding author upon reasonable request after completion of MARS-CA.

### Oversight and monitoring

#### Composition of the coordinating center and trial steering committee {5d}

The research team of MARS-CA will coordinate and manage the entire study process. It will meet regularly to discuss ongoing study questions of any type.

#### Composition of the data monitoring committee, its role and reporting structure {21a}

Due to the overall low risk of MARS-CA for its participants and the fact that MARS-CA is a rather small one site study, no data monitoring committee is needed.

#### Adverse event reporting and harms {22}

The MARS-CA research team will be in close contact with the trainee therapists who participate in the study to monitor for adverse events of the patients during the session-introducing interventions. If patients report discomfort during the interventions, they are asked to immediately get in touch with their therapists. In turn, trainee therapists are requested to report their patients’ difficulties to the MARS-CA research team. The MARS-CA research team discusses the difficulties delineated and decides if it is justifiable that the patient further participates in the study or not. Any adverse events that lead to a discontinuation of MARS-CA will be documented.

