### Trial design {8}

MARS-CA is a single-center, parallel group, three-arm randomized controlled trial. It is designed to test the effectiveness of SIMI in contrast to SIRI to no specific interventions at the beginning of therapy sessions with children and adolescents. Study participants will be randomized either to the intervention group, practicing SIMI at the beginning of the therapy sessions (IG-M), or to the active control group, practicing SIRI at the beginning of the therapy sessions (CG-R), or to the control group with no specific interventions at the beginning of the therapy sessions (CG). A flow chart through the study is shown in Fig. 1.

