### Eligibility criteria {10}

Inclusion criteria for patients participating in MARS-CA are a primary hyperkinetic disorder, depressive disorder, or anxiety disorder diagnosis. Exclusion criteria for patients are as follows: (a) age below 11 or above 19 years, (b) deficient German language skills, (c) comorbid psychotic disorder, and (d) acute suicidality. Other comorbidities are not considered as an exclusion criterion. Drop-out criteria are (a) termination of individual psychotherapy before the 24th therapy session, (b) refusal to participate in the study any longer, and (c) inability to take part in the interventions any longer (due to severe crises during the therapy process, propensity for dissociation during the interventions, etc.). Trainee therapists who want to take part in the study have to visit two workshops for study preparation.

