#### Criteria for discontinuing or modifying allocated interventions {11b}

Not applicable, no discontinuing or modifying allocated interventions envisaged.

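### The harms section commits to recording only adverse events that end participation, and ties monitoring to exercises that one arm lacks, so recorded events would understate occurrence and be ascertained unequally across arms

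*Protocol article*

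**What the plan says.** The section on adverse event reporting and harms {22} is the only place where the protocol article deals with harms. It describes a chain:

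- **Monitoring.** The research team stays in contact with the trainee therapists "to monitor for adverse events of the patients during the session-introducing interventions".
- **Patient report.** "If patients report discomfort during the interventions, they are asked to immediately get in touch with their therapists".
- **Onward report.** Therapists are requested to pass their patients' difficulties to the research team.
- **Decision.** "The MARS-CA research team discusses the difficulties delineated and decides if it is justifiable that the patient further participates in the study or not".
- **Record.** "Any adverse events that lead to a discontinuation of MARS-CA will be documented".

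Four other parts bear on this. Trial design {8} gives CG no session-introducing exercise. Eligibility criteria {10} lists, as examples of why a patient might drop out through inability to continue the interventions, severe crises in therapy and "propensity for dissociation during the interventions". The section on discontinuing or modifying allocated interventions {11b} reads "Not applicable, no discontinuing or modifying allocated interventions envisaged". Table 1 schedules no adverse event item for any arm.

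**The concern.** Two features of the stated chain distort the harms data.

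First, the commitment to document is conditional on the event's consequence. A patient who becomes distressed or dissociates during an exercise, reports it and carries on would be discussed by the team, but the plan promises no record.

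Second, both the monitoring window and the trigger for reporting are defined by the exercises. The mindfulness arm (IG-M) and the relaxation arm (CG-R) have that window up to 24 times per patient; CG never has it. A difference in recorded events between CG and the other arms would then mix a difference in risk with a difference in opportunity to be counted.

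The participants are aged 11 to 19 and have psychiatric diagnoses. The person who reports is the unblinded treating trainee, and the plan has no data monitoring committee and no independent monitoring or auditing. The absence of a committee is justified partly by low overall risk. A record confined to events that end participation could not do much to confirm that premise.

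**Working it through.** The protocol states no adverse event figure, so there is none to reproduce. The check is a reading of the sections against each other, followed by an illustration on assumed values.

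**1. What is recorded.** The harms chain has two possible ends for a reported difficulty. If participation ends, the event is documented. If participation continues, the text stops at discussion. The phrase about discontinuation of MARS-CA could in principle mean ending the trial, but the preceding sentence concerns whether the individual patient continues, so the patient reading is the natural one. On the other reading, fewer events still would be covered.

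**2. Who can be recorded, by arm.**

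- Exercise-linked monitoring and patient prompt: available in IG-M and CG-R; absent in CG, which has no exercise.
- Documentation when an event ends participation: open to all three arms, since the sentence names no arm. Early termination of therapy and refusal to continue, both drop-out criteria, apply everywhere. The third criterion is worded around the interventions and fits CG poorly.
- Scheduled adverse event enquiry: none in Table 1 for any arm.
- Symptom scales (YSR 11-18R and the three DISYPS-III self-ratings): scheduled at baseline, sessions 3, 10, 17 and 24, and follow-up, with no restriction by arm.

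So one route of three exists in only two arms, one is nominally common to all, and no scheduled enquiry makes up for the difference. The symptom scales can show deterioration, but they do not identify a discrete event, its session or its relation to an exercise.

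**3. Consistency on discontinuation.** Section {11b} says no discontinuation or modification is envisaged. Section {10} has a drop-out criterion for inability to continue the interventions, and section {22} lets the team decide against further participation. Since leaving the study is what triggers documentation, these three must agree on what counts as leaving.

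**4. Illustration, on assumed values only.** Equal randomisation gives 135/3 = 45 per arm. Let p be the proportion of patients with an event and s the share of those events that end participation. If only the committed events are recorded, the expected number recorded in an arm is 45 × p × s, and the chance that none is recorded is (1 − p × s)^45.

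- p = 0.10, s = 0.05: 4.5 affected, 45 × 0.10 × 0.05 = 0.23 recorded; chance of none = 0.995^45 = 0.80.
- p = 0.20, s = 0.10: 9.0 affected, 0.90 recorded; chance of none = 0.98^45 = 0.40.
- p = 0.30, s = 0.25: 13.5 affected, 3.38 recorded; chance of none = 0.925^45 = 0.03.

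The recorded fraction is s by construction, so these lines show the mechanism and do not estimate a loss. If an arm recorded 0 of 45, the one-sided 95% upper bound would be 1 − 0.05^(1/45) = 0.064, or 6.4%. That bound is correct for events that end participation. It is wrong only if presented as a bound on all events.

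**The case against.** The strongest reply is that the text does not forbid recording other events. It sets a reporting chain with no severity threshold, so tolerated difficulties do reach the research team, and a fuller protocol or a case report form may log them. **This stands in part.** A reader might infer that tolerated events are never recorded; the document does not say that. What it does is set out the chain from report to record and attach the commitment to one outcome only. That is a stated rule with a consequence, not merely an omitted detail.

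A reader might also infer that the CG harms record is empty by construction. The document does not support this. The documentation sentence has no arm limit, and a CG patient who leaves because of an event could be documented. Only the exercise-linked route is missing there.

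Third, worsening on the symptom scales and drop-out are collected in all arms, so it would be too strong to say that no safety signal could emerge. This stands, but those data answer a different question.

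Fourth, harms are not among the stated objectives or outcomes, the exercises last between 4 min 15 s and 7 min 30 s, they were adapted after feedback from 36 young patients, and crises and dissociation are named only as examples. All true, and they bear on how many events to expect. They do not make the recording rule neutral across arms.

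**Conclusion.** The point holds in a limited form. As written, the plan commits to documenting adverse events only when they lead to discontinuation, and defines monitoring and patient reporting by exercises that CG does not receive. Adverse events recorded under that commitment would understate occurrence whenever any event is tolerated, and would not be ascertained equally across the three arms.

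This rests on two readings: that discontinuation refers to the individual patient, and that practice follows the stated commitment without going beyond it.

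No percentage of events lost can be derived. A reader might be drawn to a figure such as 50–90%, but that is just one minus an assumed discontinuation share of 10–50%; the documents supply no such share. This is a worthwhile and inexpensive improvement to the safety data and leaves the efficacy analysis unaffected.

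**What to change.** Amend section {22} so that:

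- every adverse event or difficulty reported by a patient or therapist during the treatment period is documented in all three arms, whether or not participation ends, with arm, session number and severity;
- one identically worded adverse event question is added to the forms already completed at sessions 3, 10, 17 and 24 in all arms;
- counts are reported by arm, with the date on which the new capture began, and participants before and after that date shown separately.

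Separately, reconcile sections {10}, {11b} and {22} on discontinuation, so that the event that triggers documentation is defined once. How that is settled clinically is for the investigators.

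**Cost.** No extra visit is needed. There is slightly more paperwork, on top of patient surveys that already take 45–50 minutes per time point, and the amendment needs ethics approval before use. Recruitment began in April 2019 and was expected to finish around July 2023, so capture stays incomplete for participants already treated. That is why the two periods should be kept apart in the report.
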